### Primary outcome measure

Roland Disability Questionnaire for Sciatica (RDQ). This illness-specific 23-item functional assessment questionnaire is frequently used for low back pain and sciatica [23]. Scores range from 0 to 23, reflecting a simple unweighted sum of items endorsed by the respondent. High score reflects severe disabling pain. Recovery of pain is defined as improvement of 11 points or more from baseline [24]. This self-report measure of physical disability due to low back and leg pain has shown high level of internal consistency, construct validity, and responsiveness [24,25]. The RDQ is the main primary outcome measure in this trial.

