### Sample size

The sample size is calculated on the basis of the RDQ both at both short term and long term follow-up. A difference in effectiveness is considered clinically relevant whenever patients with nerve root decompression alone will obtain at least 20% difference in RDQ score. Instrumented spondylodesis is assumed to result in at least 60% good outcome at 12 weeks. This means that 80% of the patients treated with nerve root decompression alone should have good results in order to proof superiority of Gill's procedure. Treatment is considered to be justified in case of improvement of at least 7 points on the RDQ score; 20% difference corresponds to 8.4 points improvement on in the RDQ score. With a power of 90% and a two-tailed significance level of 0.05, 220 patients with symptomatic spondylolytic spondylolisthesis grade I and II are needed (110 patients in both treatment groups, including 10% loss to follow-up). The numbers used for this sample size calculation are retrieved from the 1 and 5-years results of the Maine Lumbar Spine Study [38,39].

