### Statistical analysis

Baseline comparability will be analysed by descriptive statistics to determine whether randomisation was successful. Whenever necessary to remove residual confounding or simply in order to increase power, adjustments for baseline variables will be performed in the analyses. Differences in outcome measures between both groups, together with 95% confidence intervals, will be calculated. We stipulate in advance that we will also analyze a model containing the interaction of follow-up time and randomisation group; if the latter is significant at the 5% level, the conclusion of "unequality of treatments" follows; if the latter is non-significant, the treatment effect will be calculated on the basis of a model without group*time interaction. All data will be analysed according to the "intention-to-treat principle". We state a priori that we will perform as a subgroup analysis, the evaluation of the interaction between the treatment allocation and both the grading of the disease (grade I versus grade II spondylolisthesis) as well as the localisation of nerve root compression (underneath the pseudo-joint or between pedicle and slipped disc). We will conclude that the treatment effect depends on the value of those variables if the interaction is significant at the 5% level. If the interaction is non-significant, we will quantify the main effect of these variables in the usual way. In addition, explorative subgroup analyses will be performed, based on the interaction between the randomization variable and various different baseline variables (table 3). Data will be stored via the internet-based secure data management system "ProMISe" of the department of Medical Statistics and Bioinformatics. The analyses will be carried out using appropriate statistical software (e.g. SPSS).

**Table 3 T3:** Selected prognostic variables for subgroup analysis

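### The stated 90% power rests on an undefined good-outcome proportion rather than on RDQ points, and the section's own translation into points does not match it

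*Protocol article*

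**What the plan says.** The Primary outcome measure section makes the RDQ, scored 0 to 23, the main primary outcome. The opening of Methods/design defines equal effectiveness as a difference of no more than 4 RDQ points.

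The Sample size section says the calculation is based on the RDQ at both short and long term. It then works with proportions: "Instrumented spondylodesis is assumed to result in at least 60% good outcome at 12 weeks", and so "80% of the patients treated with nerve root decompression alone should have good results in order to proof superiority" of Gill's procedure. It calls clinically relevant "at least 20% difference in RDQ score", adds "Treatment is considered to be justified in case of improvement of at least 7 points on the RDQ score", and equates the 20% difference with 8.4 points of improvement. No SD is given. The result is "With a power of 90% and a two-tailed significance level of 0.05, 220 patients", that is 110 per arm, said to include 10% loss to follow-up.

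Two other sections contain possible definitions of success. Under Primary outcome measure: "Recovery of pain is defined as improvement of 11 points or more from baseline". Under Perceived recovery, the top two categories of the 7-point Likert scale count as good results.

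The Statistical analysis section states: "Differences in outcome measures between both groups, together with 95% confidence intervals, will be calculated". It adds a model with a group-by-time interaction and optional adjustment for baseline variables. It names no comparison of good-outcome proportions.

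**The concern.** A power statement should describe the comparison on which the trial will be judged. Here the power is for a difference in proportions, whereas the main outcome, the equality margin and the modelling are set around RDQ points and group differences. Three consequences follow.

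- A reader of a null RDQ result would take it to come from a trial with 90% power on that scale, which the section does not show.
- The 60% and 80% cannot be attached to a variable, because good outcome is not defined where it is used and three candidates exist. In an unblinded trial, a responder cut-off left open could be chosen late.
- The section treats as clinically relevant a shift in points that Methods/design would class as equal effectiveness.

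**Working it through.** **Inputs from the protocol article.** Two-sided alpha 0.05 (z = 1.960); power 90% (z = 1.2816); rates 0.60 and 0.80; 110 per arm including 10% loss, so 110 × 0.9 = 99 evaluable; points 7 and 8.4; equality margin 4 points.

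**Inferred.** The target of 1.4 points is 8.4 − 7. The text does not state this subtraction.

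**Assumed.** RDQ SD of 5, 6 or 7 points, because the article gives none.

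**1. Reproducing the 110.** Pooled two-proportion formula, mean rate 0.70:

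n = [1.960·√(2·0.7·0.3) + 1.2816·√(0.6·0.4 + 0.8·0.2)]² / 0.20² = 108.2, rounded up to 109 per arm.

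This comes within one patient of 110, but before any loss. With 10% loss, 109/0.9 = 121.1, so 122 per arm. Other two-sided versions with loss give 118 (unpooled), 120 (arcsine) and 133 (continuity-corrected). None gives 110 including loss.

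**2. Power for the proportion.** Power = Φ{[0.20·√n − 1.960·√0.42] / √0.40}.

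- n = 110: 90.5%
- n = 99: 87.2%

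**3. Do the two scales agree?** The 20% is absolute for the rates (60 to 80) and relative for the points (7 × 1.2 = 8.4). Under a normal shift, moving from 60% to 80% above a fixed cut-off is 0.842 + (−0.253) = 0.588 SD. At SD 5, 6 or 7 that is 2.9, 3.5 or 4.1 points. It equals 1.4 points only if the SD is 1.4/0.588 = 2.4.

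**4. Power on RDQ points**, for an unadjusted comparison at one visit with 99 per arm. SE = SD·√(2/99) = 0.1421·SD; power = Φ(difference/SE − 1.960); detectable difference at 90% power = 3.2415·SE.

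| Assumed SD | SE | Power for 1.4 points | Power for 4 points | Detectable at 90% power |
|---|---|---|---|---|
| 5 | 0.711 | 50% | >99% | 2.3 |
| 6 | 0.853 | 38% | >99% | 2.8 |
| 7 | 0.995 | 29% | 98% | 3.2 |

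For 1.4 points, 90% power requires SD ≤ 1.4/(3.2415 × 0.1421) = 3.04, or 3.20 with 110 per arm. At SD 4 the power is 69%.

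**5. Effect of a more efficient analysis**, 1.4 points, assumed correlation of 0.5 between all measurements, SD 5/6/7:

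- single visit with baseline adjustment (SD × √0.75): 62/47/37%
- six visits to week 104 (3, 6, 12, 26, 52, 104) pooled, unadjusted (SD × √(3.5/6)): 73/58/45%
- six visits pooled and adjusted (SD × √(3.5/6 − 0.25)): 93/81/68%

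The pooled figures also assume a constant effect over time.

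**6. The 80% as a success criterion.** With 99 per arm and 60% observed in the fusion arm, the pooled z-test first reaches 1.96 at a gap of about 13 percentage points. An observed 80% is therefore not needed for significance.

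**The case against.** The strongest reply is that low power for 1.4 points does little harm here. The protocol calls anything up to 4 points equal, and a 4-point difference has at least 98% power at SD 5 to 7 even in the least efficient analysis. That stands. A reader might infer from the table that the trial has only 29% to 50% power for its primary comparison. The documents do not support this: the SD is assumed, 1.4 is inferred, and the Statistical analysis section allows baseline adjustment and, if the interaction is not significant, an effect from a model without it. Step 5 shows how far that could raise power.

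Three further tempting readings also go too far.

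- *That the proportion is never tested.* The analysis sentence is generic and could cover a dichotomised outcome, and a condensed article may leave such detail to a fuller plan. What can be said is that no such test is named.
- *That 7 and 11 points contradict each other.* They carry different labels: treatment being justified, and recovery of pain. Neither is called good outcome. The defect is an undefined term with competing candidates.
- *That the sentence on 80% is simply an error.* In context it gives the design alternative, and it is the only place where the 80% appears. It is loosely worded, not to be deleted.

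The reply does not remove the mismatch itself. The section claims an RDQ basis and states a power that its RDQ figures do not produce.

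**Conclusion.** The point holds as a defect in how the power is stated, not as proof of an underpowered trial. Three findings need no assumed SD:

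- the 110 per arm corresponds to 60% versus 80% on an undefined endpoint, for which no test is named;
- with the stated 10% loss, power for that comparison is about 87%, not 90%;
- the 1.4-point reading of 7 versus 8.4 falls inside the protocol's own 4-point equality band.

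The scale mismatch in step 3 rests on a normal shift. The powers of 50%, 38% and 29% for 1.4 points, and the detectable differences of 2.3 to 3.2 points, hold only for assumed SDs of 5 to 7, a single visit, no adjustment and 99 per arm. On the same assumptions the sample is ample for a 4-point difference.

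**What to change.** Reword the Sample size section and align the related sections.

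1. State that the primary comparisons at 12 weeks and 2 years are of mean RDQ.
2. Give the power for those comparisons with the SD named as an assumption: with 99 evaluable per arm, about 90% for 2.3 to 3.2 points at SD 5 to 7, unadjusted.
3. Remove the 7-versus-8.4 translation or reconcile it with the 4-point margin, and say whether 20% is absolute or relative.
4. Define good outcome by one named threshold, use it consistently across the Sample size and outcome sections as a secondary responder outcome, and give its power as about 87% for 60% versus 80% after 10% loss.
5. Reword the 80% as the assumed rate under the alternative, not a result that must be observed.

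The cost is some redrafting and a slightly less favourable power statement. No extra patients are needed.

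### The 110 patients per arm are said to cover 10% loss to follow-up, but 60% versus 80% at 90% power needs 106 to 109 evaluable per arm, so power after the planned loss is about 87%

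*Protocol article*

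**What the plan says.** All the inputs are in the Sample size section of the protocol article. The comparator rate is a minimum: "Instrumented spondylodesis is assumed to result in at least 60% good outcome at 12 weeks". The rate required in the other arm is named: "80% of the patients treated with nerve root decompression alone should have good results in order to proof superiority of Gill's procedure". The error rates are given by "With a power of 90% and a two-tailed significance level of 0.05". The result is stated as "220 patients with symptomatic spondylolytic spondylolisthesis grade I and II are needed (110 patients in both treatment groups, including 10% loss to follow-up".

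The section also expresses the effect in points on the Roland Disability Questionnaire (RDQ). An improvement of 7 points justifies treatment, and "20% difference corresponds to 8.4 points improvement on in the RDQ score". It gives no standard deviation and names no formula. It attributes its numbers to the 1-year and 5-year results of an earlier cohort study.

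**The concern.** The section prints two proportions, a power, a two-sided level, a loss rate and a resulting number, so the number can be checked directly. For 60% versus 80% it looks like the unadjusted evaluable number, although the text says it already contains the allowance for loss. If so, the stated 90% power holds only if nobody is lost. Under the plan's own 10% loss the trial has less power than stated, and those running it would believe in a margin against attrition that does not exist.

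**Working it through.** **Inputs (all from the Sample size section).** p1 = 0.60, p2 = 0.80, difference 0.20, mean 0.70. Two-sided 0.05 gives z = 1.960; 90% power gives z = 1.2816. Allocation is 1:1, with 110 randomised per arm and 10% loss.

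**Step 1. Evaluable patients needed per arm.**

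- Pooled variance under the null: [1.960 × √(2 × 0.70 × 0.30) + 1.2816 × √(0.24 + 0.16)]² / 0.20² = (1.2702 + 0.8106)² / 0.04 = 108.2, so 109.
- Unpooled variance: (1.960 + 1.2816)² × (0.24 + 0.16) / 0.04 = 10.507 × 10 = 105.1, so 106.
- Arcsine: 107.5, so 108.

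**Step 2. Can the plan's figure be reproduced?** Without any loss, yes: the pooled formula gives 109, and 110 evaluable per arm give 90.5% power. With the loss included, as the text states, no:

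| Formula | Evaluable per arm | n / 0.9 | n × 1.1 |
|---|---|---|---|
| Unpooled | 106 | 118 | 117 |
| Arcsine | 108 | 120 | 119 |
| Pooled | 109 | 122 | 120 |

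Even the more lenient n × 1.1 stays above 110. By n / 0.9 the total is 2 × 118 = 236 to 2 × 122 = 244. A continuity correction, which the article does not mention, would widen the gap: 119 evaluable and 133 randomised per arm.

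**Step 3. Other readings of the inputs.** For 60% versus 80%, numbers per arm after loss (n / 0.9):

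- two-sided, 80% power: 92, or 102 with continuity correction;
- one-sided 0.05, 90% power: 99, or 109 with continuity correction.

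Only the last comes near 110, and it contradicts the stated two-tailed level.

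**Step 4. Power after the planned loss.** 110 × 0.9 = 99 evaluable per arm.

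- Pooled: z = [0.20 − 1.960 × √(0.42/99)] / √(0.40/99) = (0.2000 − 0.1277) / 0.0636 = 1.138, so power 87.2%.
- Unpooled: z = 0.20/0.0636 − 1.960 = 1.186, so power 88.2%.
- Arcsine: 87.5%.
- Exact binomial power of the uncorrected chi-square test: 87.7%. With continuity correction: 83.9%.

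If the loss is instead read as 110 / 1.1 = 100 evaluable per arm, power is 87.6% (pooled) or 88.5% (unpooled).

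**Step 5. The RDQ-points route.** The difference between 8.4 and 7 points is 1.4. The number per arm is 2 × 10.507 × SD² / 1.4². The article gives no SD, so any value is an assumption: SD 3 gives 97 evaluable per arm, SD 4 gives 172 and SD 5 gives 269. An SD of about 3.0 would be needed to arrive at 99. The 60% versus 80% contrast is therefore the only fully specified basis.

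**The case against.** The strongest reply is that the basis of the 110 is inferred. The section says the size rests on the RDQ at short and long term, mixes points with percentages, and draws on an outside study without showing a formula. A points-based calculation could have been used. The 4-point limit for equal effectiveness in Methods/design would need 99 evaluable per arm at an SD of about 8.7, and fewer at any smaller SD. This much stands: how the authors reached 110 cannot be known from the article. But the Sample size section does not cite the 4-point limit, and no SD is given that would support either points-based route.

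Second, 60% is stated as a floor. With the same 20-point difference, 64% versus 84% needs 99 evaluable per arm, which is 110 after 10% loss. That pair would fit, but the text names 80% as the rate to be reached, so 60% versus 80% is what it says.

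Third, the Statistical analysis section plans models with follow-up time and baseline adjustment, and the RDQ is measured repeatedly. The planned analysis may therefore recover some power, and patients lost late may still contribute data. This is fair, and the 87% is the power of the simple planning comparison only. The stated sample size does not, however, rest on any such gain.

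Fourth, the gap is small, and no continuity-corrected test is planned. Both are true. The corrected figures above are shown only as a variant, and the conclusion does not use them.

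**Conclusion.** The point holds. On the inputs printed in the Sample size section, 110 per arm is about the evaluable number, and it does not also absorb 10% loss. The shortfall is 8 to 12 patients per arm (118 to 122 against 110), or about 2 to 3 percentage points of power: 87.2% to 88.2% instead of 90%. The risk of missing a true 60% versus 80% difference becomes 11.8% to 12.8% instead of 10%.

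This rests on three things: the proportions are the planning basis, the test is two-sided without continuity correction, and the 10% loss leaves 99 evaluable per arm. It is a correctable misstatement of power and does not invalidate the design.

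**What to change.** State the formula and inputs behind the 110, remove the claim that 10% loss is included, and give the power on both bases, for example: *For 60% versus 80% good outcome at a two-sided 0.05 level, 220 patients (110 per arm) give 90% power if all are evaluable; with 10% loss to follow-up (99 per arm) the power is about 87%.* This costs one sentence and a stated power about 3 points less favourable, with no extra patients and no change to procedures.

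If 90% power after loss is to be kept, about 236 to 244 patients must be randomised, which is 16 to 24 more than planned. If the 110 came from another calculation, such as one on RDQ points, the article should give that calculation with its SD, and the loss statement should be checked against it.

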### Statistical analysis

Baseline comparability will be analysed by descriptive statistics to determine whether randomisation was successful. Whenever necessary to remove residual confounding or simply in order to increase power, adjustments for baseline variables will be performed in the analyses. Differences in outcome measures between both groups, together with 95% confidence intervals, will be calculated. We stipulate in advance that we will also analyze a model containing the interaction of follow-up time and randomisation group; if the latter is significant at the 5% level, the conclusion of "unequality of treatments" follows; if the latter is non-significant, the treatment effect will be calculated on the basis of a model without group*time interaction. All data will be analysed according to the "intention-to-treat principle". We state a priori that we will perform as a subgroup analysis, the evaluation of the interaction between the treatment allocation and both the grading of the disease (grade I versus grade II spondylolisthesis) as well as the localisation of nerve root compression (underneath the pseudo-joint or between pedicle and slipped disc). We will conclude that the treatment effect depends on the value of those variables if the interaction is significant at the 5% level. If the interaction is non-significant, we will quantify the main effect of these variables in the usual way. In addition, explorative subgroup analyses will be performed, based on the interaction between the randomization variable and various different baseline variables (table 3). Data will be stored via the internet-based secure data management system "ProMISe" of the department of Medical Statistics and Bioinformatics. The analyses will be carried out using appropriate statistical software (e.g. SPSS).

**Table 3 T3:** Selected prognostic variables for subgroup analysis

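### The group*time rule attaches a verdict to one 5% test and leaves a second 5% look open; if both are used, some difference is falsely declared in about 9.75% of trials.

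*Protocol article*

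**What the plan says.** The Statistical analysis section of the protocol article announces the rule in advance: "We stipulate in advance that we will also analyze a model containing the interaction of follow-up time and randomisation group". It then sets out two branches.

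- **Interaction significant:** "if the latter is significant at the 5% level, the conclusion of 'unequality of treatments' follows".
- **Interaction not significant:** "if the latter is non-significant, the treatment effect will be calculated on the basis of a model without group*time interaction".

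The same section says that group differences in the outcome measures will be given with 95% confidence intervals. It sets no threshold and attaches no conclusion to the effect from the reduced model.

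The Sample size section gives the only error level for the main comparison: "With a power of 90% and a two-tailed significance level of 0.05". It also says what the trial is meant to show: "80% of the patients treated with nerve root decompression alone should have good results in order to proof superiority of Gill's procedure". The introduction to Methods/design hypothesises that Gill's procedure is better at 12 weeks and equal at 2 years, where equal means at most 4 RDQ points apart. The article does not link the two branches to these two claims. It does not divide the 5% between the branches or name one of them as the only confirmatory step.

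**The concern.** Either branch can end in the statement that the operations differ. A significant interaction gives that verdict outright. A non-significant one leads to an average effect whose 95% interval excludes zero exactly when a two-sided 5% test rejects. A non-significant first step does not protect the second, because the interaction and the average effect carry separate information. A team that follows the rule in this way has two chances at 5% each. A borderline result at either step would be reported as significant at 5%, although the procedure that produced it errs nearly twice as often.

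**Working it through.** **Inputs.** From the Statistical analysis section: 5% for the interaction test and 95% intervals for differences. From the Sample size section: two-tailed 0.05, 90% power, 60% versus 80% good outcome, 110 per arm. Assumption: the second-step interval is read as a two-sided 5% test.

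**1. The plan's own figure.** With a mean proportion of 0.70, the usual formula for two proportions gives

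n = [1.960·√(2·0.70·0.30) + 1.282·√(0.60·0.40 + 0.80·0.20)]² / 0.20² = 108.2, so 109 per arm.

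This agrees with 110 per arm before any loss. Allowing for 10% loss gives 109/0.9, so 122 per arm. The statement that 110 already includes the loss is therefore not reproduced. That is a separate matter and nothing below rests on it. What matters here is that the design figure uses a single two-sided 5% test.

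**2. Are the two steps independent?** Let d be the vector of arm differences over the visits, with covariance V. The reduced-model (generalised least squares) effect weights d by w proportional to V⁻¹1. With time as a category, the interaction uses contrasts A·d whose rows sum to zero. Their covariance with the effect is proportional to A·V·V⁻¹·1 = A·1 = 0. Under normality the two are independent.

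**3. Overall rate with no difference at any time.**

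- Step 1: 0.05.
- Step 2, reached in the other 95%: 0.95 × 0.05 = 0.0475.
- Sum: 0.0975 = 1 − 0.95². Without independence the bound is 0.05 + 0.05 = 0.10.

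**4. Simulation check.** The settings were 99 per arm (110 less 10%), 2 or 6 visits, time linear or categorical, three covariance structures, and 200,000 replicates each.

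| Second-step estimator | Overall rate |
|---|---|
| Generalised least squares | 9.65% to 9.84% |
| Simple average over visits | 9.25% to 9.76% |

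With generalised least squares, the second-step rate given a non-significant interaction stayed near 5.0%. The covariance structures were assumed, but the result hardly depends on them.

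**5. The directional error.** A second-step result that falsely favours Gill's procedure has probability 0.95 × 0.025 = 2.4%.

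**6. Power under the possible repairs.** A two-sided 5% test with 90% power has a standardised effect of 1.960 + 1.282 = 3.242.

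- *2.5% at each step.* Overall error is 1 − 0.975² = 4.94%. Second-step power is Φ(3.242 − 2.241) = 84%. For 60% versus 80%, power at 2.5% is 84.6% with 110 per arm and 80.2% with 99; at 5% these are 90.5% and 87.2%. Keeping 90% at 2.5% needs 129 evaluable per arm.
- *One joint 5% test of group plus group by time.* Against a constant difference the noncentrality is 3.242² = 10.51. With two time points (2 degrees of freedom, critical value 5.99) power is about 84%. With six visits as categories (6 degrees of freedom, critical value 12.59) it is about 67%.

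**The case against.** The strongest objection is that the second step is not written as a test. The effect is to be calculated, and only the first step carries a verdict. If the second step is estimation alone, the rule spends 5% and no more. This stands as far as the wording goes, so the 9.75% has to be conditional. It does not remove the point. On that reading the rule contains no test of a constant difference, in a trial whose stated aim is to prove superiority. The interval would almost certainly be read as one.

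A reader might also infer that the article promises a 5% family-wise level and breaks it. It does not: the 0.05 belongs to the sample size calculation and is never described as covering the sequence of models.

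A reader might further infer that Gill's procedure would be falsely called superior in one trial in ten. The documents do not support that either. An interaction verdict of inequality has no direction, and the false-favour rate at the second step is about 2.4%.

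Finally, multiplicity is often left to an analysis plan, and that plan is not shown. The absence of an alpha split is therefore not a fault in itself. The fair criticism is of what the article does fix: a 5% threshold with a conclusion attached, followed by an unprotected second look. The word also in the rule may mean that the interaction model was intended as supplementary, but a supplementary analysis should not settle whether the treatments are equal.

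**Conclusion.** The point holds conditionally. If the second-step interval is used to conclude that the arms differ, the rule declares some difference in about 9.75% of trials in which there is none at any time. The bound is 10%, so the rate is nearly double the 5% used to size the trial. About half comes from each step. This assumes two valid 5% tests and no difference at any visit. It does not depend on the standard deviation, the within-patient correlation or the number of visits. If the second step is estimation only, the rate is 5%. The article does not say which is meant, and the wording should settle it. The weakness should be corrected but does not invalidate the trial.

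**What to change.** **Preferred.** State that the group-by-time test is supportive and that no conclusion about equality follows from it. Take the confirmatory 12-week RDQ difference, at two-sided 5%, from the repeated-measures model that keeps the interaction. Take the 2-year contrast from the same model and judge it by its confidence interval against the plan's 4-point RDQ margin. A second test for a difference would not answer the 2-year hypothesis of equality. The change is one of wording and keeps the full 5% for the 12-week comparison. The cost is that a significant interaction alone no longer supports a conclusion, and the confirmatory test does not pool over visits.

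**If one global verdict of inequality is wanted.** Use a single joint test of group plus group by time at 5%. It restores the error rate, but it has less power against a constant difference: about 84% with two time points where a single-contrast test has 90%, and less with more visits. It should therefore be limited to the two main time points.

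**Less attractive.** Keep both steps at 2.5% each, with a 97.5% interval at the second. Power falls from a nominal 90% to about 84%, or to about 80% with 99 evaluable per arm, and two different findings would still carry the same verdict.

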**Methods/design:**

All patients (age between 18 and 70 years) with sciatica or neurogenic claudication lasting more than 3 months due to spondylolytic spondylolisthesis grade I or II, are eligible for inclusion. Patients will be randomly allocated to nerve root decompression according to Gill, either unilateral or bilateral, or pedicle screw fixation with interbody fusion. The main primary outcome measure is the functional assessment of the patient measured with the Roland Disability Questionnaire for Sciatica at 12 weeks and 2 years. Other primary outcome measures are perceived recovery and intensity of leg pain and low back pain. The secondary outcome measures include, incidence of re-operations, complications, serum creatine phosphokinase, quality of life, medical consumption, costs, absenteeism, work perception, depression and anxiety, and treatment preference. The study is a randomised prospective multicenter trial in which two surgical techniques are compared in a parallel group design. Patients and research nurse will not be blinded during the follow-up period of 2 years.

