## Methods/design

We designed a multicenter randomised controlled cost-effectiveness trial on the treatment of low-grade spondylolytic spondylolisthesis in which two surgical techniques are compared in a parallel group design. The primary outcome measure is the Roland Disability Questionnaire (RDQ) for sciatica. The follow-up period will last 2 years (with extension to 5 years). In order to collect enough patients, a multicenter design is necessary. The study protocol is approved in all participating hospitals by the Medical Ethics Committee.

We hypothesise that nerve root decompression according to Gill is more (cost-)effective on the short term (12 weeks) and equally (cost-)effective on the long term (2 years). Equal effectiveness is defined as maximal 4 points difference on the RDQ score between decompression and instrumented fusion. Moreover, we will identify subgroup of patients who may benefit more of one of the allocated treatments.

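### The group-by-time decision rule does not answer the two questions the hypothesis poses, at 12 weeks and at 2 years

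*Protocol article*

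**What the plan says.** The abstract's Methods/design paragraph gives the main primary outcome as function, "measured with the Roland Disability Questionnaire for Sciatica at 12 weeks and 2 years". The Methods/design section hypothesises that Gill's procedure is "more (cost-)effective on the short term (12 weeks) and equally (cost-)effective on the long term (2 years"). A separate sentence there sets the limit for the second part: "Equal effectiveness is defined as maximal 4 points difference on the RDQ score between decompression and instrumented fusion".

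The Statistical analysis section begins with a general statement: "Differences in outcome measures between both groups, together with 95% confidence intervals, will be calculated". It then adds a second model, one with a group-by-time term, and fixes beforehand what its result will mean. For a significant term the article states: "if the latter is significant at the 5% level, the conclusion of 'unequality of treatments' follows". For the opposite result the instruction is different: "if the latter is non-significant, the treatment effect will be calculated on the basis of a model without group*time interaction". The section names neither of the two primary time points and does not mention the 4-point limit.

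**The concern.** The hypothesis asks two separate questions: superiority at 12 weeks, and a difference within 4 points at 2 years. The natural picture behind it is an early advantage that fades. The rule asks a third question, whether the group difference changes over time, and uses the answer in two ways.

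- If the interaction is significant, the verdict is that the treatments are unequal. That verdict does not say which treatment is better, when, or by how much.
- If it is not significant, one effect common to all visits replaces the two contrasts of interest. A significance test on the same data has then chosen the model.

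This is the only place in the section where a conclusion on equality is attached to a result. Followed as written, the trial could return the same verdict for an early benefit that fades to nothing and for one that reverses. It could otherwise report an average that describes neither primary time point.

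**Working it through.** The article gives no operating characteristics for this rule, so there is no stated figure to reproduce.

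**Inputs from the article.** 110 patients per arm including 10% loss (Sample size), so 110 × 0.9 = 99 evaluable per arm. Interaction tested at 5%. Equality limit 4 RDQ points. One reading of the Sample size section gives an RDQ difference of 8.4 − 7 = 1.4 points.

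**Assumed inputs.** RDQ SD 5 to 8, within-patient correlation ρ 0.3 to 0.7, early benefits of 2 and 3 points besides 1.4, and no difference at 2 years. The article gives no SD or correlation. Negative values favour Gill.

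**Step 1: how often inequality is declared (12 weeks and 2 years only).**

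SE of the change in effect = SD × √(2/n) × √(2(1 − ρ)).

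At SD 6 and ρ 0.5 this is 6 × √(2/99) × √1 = 0.853. With d the early effect, power is approximately Φ(|d|/SE − 1.96):

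- −3 fading to 0: 3/0.853 = 3.52; Φ(1.56) = 94%.
- −2 fading to 0: 2/0.853 = 2.35; Φ(0.39) = 65%.
- −1.4 fading to 0: 1.4/0.853 = 1.64; Φ(−0.32) = 38%.

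Over the assumed grid:

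| 12-week benefit, 0 at 2 years | SD 8, ρ 0.3 | SD 6, ρ 0.5 | SD 5, ρ 0.7 |
|---|---|---|---|
| 1.4 points | 18% | 38% | 72% |
| 2 points | 32% | 65% | 95% |
| 3 points | 61% | 94% | 100% |

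**Step 2: what the verdict distinguishes.** Six visits from week 3 to week 104 were simulated (5-df Wald test, 20,000 runs, SD 5 to 7, ρ 0.3 to 0.7).

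- A 3-point benefit to week 12 that fades to 0 by week 52 gave a significant interaction in 88-100% of runs.
- Gill 3 points better early but 5 points worse at 2 years, which breaches the limit, gave one in about 100%.

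The verdict is the same whether 2-year equality holds or fails.

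**Step 3: what the pooled effect estimates.** Take −2 at 12 weeks and 0 at 2 years, SD 6, ρ 0.5, two visits.

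- Pooled mean: (−2 + 0)/2 = −1, which is 1 point away from each true contrast.
- Variance at one visit: 36 × 2/99 = 0.727.
- Pooled variance: 0.727 × (1 + 0.5)/2 = 0.545, so SE = 0.739 and the 95% half-width is 1.96 × 0.739 = 1.45.
- Coverage of 0: Φ((1.45 + 1)/0.739) − Φ((−1.45 + 1)/0.739) = Φ(3.31) − Φ(−0.61) = about 73%. By symmetry, coverage of −2 is the same.

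With equal variances at the two visits, the average and the change are independent. The 73% therefore also holds among trials with a non-significant interaction.

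**The case against.** Several stronger readings are tempting, and the article does not support them.

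- **That the hypothesis implies an interaction by construction.** It does not. Equality allows up to 4 points, so a constant Gill benefit below that limit is better at 12 weeks and equal at 2 years with no interaction. The rule then pools and loses little.
- **That the rule wrongly rejects 2-year equality.** Treatments whose effects differ over time are, over the whole course, literally unequal. The text does not say that the verdict refers to 2 years. The fault is that it is uninformative about 2 years, not that it is a false statement about them.
- **That a constant 5-point difference would be missed, because it gives a significant interaction only about 5% of the time.** A non-significant interaction does not lead to a conclusion of equality. The plan then calculates the effect, and would estimate those 5 points correctly.
- **That the plan as a whole cannot answer its questions.** The interaction model is an additional analysis, and the general sentence on differences with 95% confidence intervals leaves room for estimates at each visit.
- **That the missing test against the margin is itself a fault.** A condensed article may leave that to an analysis plan.

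The size is also open to argument. The pooled bias in the example is 1 point on a 0-23 scale, a quarter of the margin, and with a small early effect the inequality verdict appears only part of the time.

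All of this stands as a limit on the claim. It does not remove the mismatch. The general sentence is tied to no time point, margin or conclusion, and the article does not say which prevails if visit-specific estimates and the rule point in different directions. Nor is this a missing detail: the rule is stipulated in advance, so an analysis plan would either inherit it or contradict it.

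**Conclusion.** The concern holds in a limited form. The rule does not match the hypothesis or the two primary time points when the treatment effect changes over time. Its significant branch cannot separate better early and equal late from better early and worse late. Its non-significant branch lets a pre-test choose a model whose single effect is biased for both contrasts.

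That mismatch follows from the text alone; the sizes in the working depend on the assumed SD, correlation and effect pattern. Under a fading benefit, the chance of an inequality verdict runs from about one in five (1.4 points, least favourable assumptions) to near certainty (3 points, most favourable). If the benefit is constant, the rule costs little.

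**What to change.** Keep the group-by-time term, with time as categories, in the repeated-measures model whatever its p-value. Base the conclusions on two pre-stated contrasts from that model:

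1. the group difference in RDQ at 12 weeks, tested for superiority at two-sided 5%;
2. the group difference in RDQ at 2 years, with its 95% confidence interval set against the stated 4-point limit.

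Delete the rule that derives inequality from the interaction and the step that drops the term. Report the interaction p-value descriptively.

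This changes analysis wording only and needs no new data or patients. The cost is precision. In the two-visit example (SD 6, ρ 0.5), the half-width at one visit is 1.96 × √0.727 = 1.67 points against 1.45 for the average, about 15% wider. The gap grows if more visits would have been averaged.
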